**Methods:**

Patients will be recruited in the regions of Andalusia, Murcia, and Valencia (Spain). Patients will remain confined to their homes, and there, they will carry out their assigned exercise program, which will be controlled telematically. Evaluators will attend to carry out all measurements at the beginning, during, and end of the study, telematically controlled. The patients will be randomly divided into three groups, two of them will perform a home exercise program (breathing exercises or non-specific exercises for muscle toning) and the third group will perform sedentary activities, using mental activation techniques, and will act as a sham group. We will evaluate respiratory variables and other variables of the physical state through physical tests, effort, and perceived fatigue. The data will be statistically analyzed, and the hypotheses will be tested between the groups, using the SPSS software, v.24, considering a 95% confidence interval.

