### Sampling and sample size calculation

The sampling of our research will be non-probabilistic, since we will contact the patients through social networks, and not the entire population belongs to these networks, so the selection of the sample will be possible only among those who voluntarily respond to our request.

The sample size will be calculated using the Granmo calculator v.7.12, based on the minimum clinically important differences in VASF [43], and estimating an alpha risk of 5% (0.05), a beta risk of 10% (0.10), in a unilateral contrast, a typical deviation of 12.5% (0.125), a minimum difference to detect of 10% (0.10), and a rate of follow-up losses of 15%, for which 32 subjects are required in each group, assuming that there are three groups. If the rate of loss to follow-up were observed greater than 15%, we will perform an intention-to-treat analysis. Finally, we will include 114 patients who will be divided into three groups, each group of at least 38 subjects, being able to overcome this value to assume the possible loss of follow-up.

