### Statistical analysis

The statistical analysis will be carried out through the IBM-SPSS Statistics 24 software, considering the Kolmogorov-Smirnov test as the standard normality test. We will analyze the intragroup hypothesis contrast inference by Student’s *t* test for paired variables with parametric distributions and Kruskal-Wallis *H* for non-parametric distributions. We will analyze the intragroup hypothesis contrast inference by one-factor ANOVA in the case of parametric distributions and Kruskal-Wallis *H* for non-parametric distributions. We will apply a posteriori analysis (post hoc) through Bonferroni’s contrast for parametric distributions and Mann-Whitney’s *U* for non-parametric ones. The confidence level used will be 95% (0′05), and the power of the study will be 90% (0′1). If the rate of loss to follow-up were observed greater than 15%, we will perform an intention-to-treat analysis.

A sub-analysis will be carried out, depending on the age of the patients, sex, and autonomous community of residence.

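### The 90% power belongs to a one-sided, unadjusted two-group test; the planned Bonferroni pairwise contrasts have about 78% to 85% at the planned enrolment

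*Protocol article*

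**What the plan says.** Under Sampling and sample size calculation, the protocol article bases the calculation on the fatigue scale (VASF) and gives "an alpha risk of 5% (0.05), a beta risk of 10% (0.10), in a unilateral contrast", with "a typical deviation of 12.5% (0.125"), a difference to detect of 0.10 and 15% losses. It reports 32 subjects per group and says that this assumes three groups. The same paragraph then sets enrolment at 114 patients, at least 38 per group.

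Under Statistical analysis, the article plans a one-factor ANOVA when distributions are parametric and Kruskal-Wallis otherwise. For the pairs it says: "We will apply a posteriori analysis (post hoc) through Bonferroni’s contrast for parametric distributions". Mann-Whitney is named for the non-parametric case, with no correction stated. The section puts the confidence level at 95% and adds "the power of the study will be 90" per cent. It does not say whether the contrasts are one- or two-sided. It labels the ANOVA intragroup, the same word that it uses for the paired t test. I read the ANOVA as the between-group comparison, since post hoc contrasts between groups make sense only there.

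**The concern.** The sample size and the analysis describe different tests. The calculation has one direction, two means and the whole 5% spent on one comparison. The analysis has an F test without direction, then three pairwise contrasts that share the 5%. Nothing in the article links the two, and the same 90% appears in both sections.

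The trial's questions are largely pairwise. The secondary objective sets the respiratory programme against the toning programme and against sham. The sham group is later to receive whichever exercise programme did better. If a pairwise contrast on fatigue is not significant, a reader will take it as the result of a comparison with a 10% chance of missing a 10-point difference. The true chance is higher.

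**Working it through.** **Inputs, all from Sampling and sample size calculation unless noted.** Difference 0.10; SD 0.125; standardised difference 0.10/0.125 = 0.8; alpha 0.05, one-sided; power 0.90; losses 15%; planned 38 per group. From Statistical analysis: Bonferroni contrasts. Three arms give three pairs, so 0.05/3 = 0.0167 per pair.

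**1. Reproducing 32.** n = 2(z_alpha + z_beta)²/0.8² = 2(1.645 + 1.2816)²/0.64 = 26.8, so 27. Then 27/0.85 = 31.8, so 32, an exact match. The alternatives tried do not give 32:

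| Basis (90% power) | Evaluable per group | After 15% losses |
|---|---|---|
| One-sided 0.05, one pair | 27 | 32 |
| Two-sided 0.05, one pair | 33 | 39 |
| One-sided 0.05/3 | 37 | 44 |
| Two-sided 0.05/3 | 43 | 51 |
| Omnibus F, third arm midway | 41 | 49 |
| Omnibus F, two arms equal | 31 | 37 |

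**2. Sample size to use for power.** The article plans 38 per group. With 15% losses, 38 × 0.85 = 32.3, so 32 evaluable. With no losses, 38. (Since 32/0.85 = 37.6, rounded up to 38, losses seem to have been allowed for twice. This narrows the gap but does not close it.)

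**3. Power of a two-sided Bonferroni contrast.** Noncentrality = 0.8 × √(n/2), with pooled three-arm degrees of freedom 3n − 3.
- n = 32: 0.8 × √16 = 3.20; critical t on 93 df = 2.438; power 77.5%.
- n = 38: 0.8 × √19 = 3.487; critical t on 111 df = 2.431; power 85.3%.

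The miss rate is therefore 22.5% and 14.7%. Requiring a significant F test as well changes little: 77% and 85% by simulation.

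**4. Difference detectable with 90% power by that contrast.** Standardised 0.933 and 0.854; times 12.5 this is 11.7 and 10.7 points.

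**5. Other readings of the analysis** (noncentral t or F):

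| Test for a 10-point difference | 32 evaluable | 38 evaluable |
|---|---|---|
| One-sided 0.05, one pair | 94% | 96% |
| Two-sided 0.05, one pair | 88% | 93% |
| One-sided Bonferroni | 85% | 91% |
| Two-sided Bonferroni | 78% | 85% |
| Omnibus F, third arm midway | 81% | 88% |
| Omnibus F, two arms equal | 91% | 95% |

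For the F test, noncentrality is n times the sum of squared deviations of the standardised means. That sum is 0.32 for means 0, 0.4, 0.8 (10.24 and 12.16), and 0.427 for means 0, 0, 0.8 (13.65 and 16.21).

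**6. What drives the loss.** With 32 evaluable, going from one-sided to two-sided costs about 5 points (94% to 88%, from 93.6% and 88.3% unrounded). The Bonferroni adjustment costs about 11 more (88.3% to 77.5%). With 38 the steps are about 3 and 8 points.

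**The case against.** Several points on the other side stand.

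- The article speaks of the power of the study, not of each contrast. The omnibus F test exceeds 90% at the planned enrolment if two arms are equal and the third differs by the full 10 points. A reader might infer that 90% is missed by every planned test; the figures do not support that.
- Two-sided contrasts are an assumption. A one-sided Bonferroni contrast reaches 91% with no losses, though only 85% with the 15% losses that the plan itself expects. A reader might take the Abstract's phrase "considering a 95% confidence interval" as proof of two-sidedness. It is not: the Statistical analysis section equates 95% with 0.05, which merely restates the 5% level.
- The Bonferroni level applies only to the parametric branch. No correction is stated for Mann-Whitney, so the uncorrected 88% and 93% are the nearer, if rough, guide there.
- A reader might compute power from the 32 per group in the calculation, that is 27 evaluable, and find 69% and a miss rate of 31%. The same paragraph supersedes that number by enrolling 38 per group.
- A statistical analysis plan that is not shown may name one primary contrast. That would settle which test matters, but the article's two sections would still disagree as printed.

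What does not stand is the idea that 38 per group closes the gap. The two-sided Bonferroni contrast stays below 90% even with no losses. Nor does the phrase about three groups rescue the calculation, since no three-group adjustment entered the number.

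**Conclusion.** The concern holds for the pairwise comparisons. The stated 90% describes a test that the analysis section does not plan, and the planned contrast has a miss rate of about 15% to 23% in place of 10%. This rests on the plan's own difference and SD, 38 randomised per group with losses between none and 15%, the parametric branch, two-sided contrasts, and the ANOVA read as between-group. That the calculation used two groups is inferred from the exact arithmetic match; the article does not say so.

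The point concerns how the trial's sensitivity is reported. It does not touch type I error, allocation or the estimates. Nor does it show that more patients must be recruited. The article gives recruitment as ending on April 30, 2020 and cites case counts to May 24, 2020, so enrolment had probably closed.

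**What to change.** 1. In Sampling and sample size calculation, state that 32 came from a one-sided, unadjusted comparison of two groups, or recalculate it for the planned analysis. Do not simply delete "in a unilateral contrast": those words are what make 32 reproducible. Without them the remaining inputs read as two-sided and give 33, or 39 after losses.
2. In both sections, replace the 90% with the power of the planned analysis. For example: with 38 randomised and 32 evaluable per group, a two-sided Bonferroni-corrected pairwise VASF contrast has about 78% power for a 10-point difference (SD 12.5), and 90% power for about 11.7 points.
3. State the assumed sidedness, and that this power applies to the parametric branch.

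The cost is wording only, with no extra patients. The drawback is that the stated power becomes less favourable.

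### The 90% power comes from a one-sided two-group formula; with 38 per arm the planned Bonferroni contrasts have about 78% power after 15% loss (85% with none)

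*Protocol article*

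**What the plan says.** Under Sampling and sample size calculation, the protocol article bases the number on the minimum clinically important difference in fatigue (VASF), with alpha 5% and beta 10%, "in a unilateral contrast, a typical deviation of 12.5% (0.125), a minimum difference to detect of 10% (0.10"). With a loss to follow-up of 15%, this is the calculation "for which 32 subjects are required in each group, assuming that there are three groups". The same paragraph then sets the enrolment: "Finally, we will include 114 patients who will be divided into three groups, each group of at least 38 subjects". It adds that the arms may exceed this to absorb losses.

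Under Statistical analysis, the comparison is by "one-factor ANOVA in the case of parametric distributions", with Bonferroni post hoc contrasts at the 95% confidence level (rank-based tests if the data are not normal). The section names no one-sided test, and it states that "the power of the study will be 90% (0′1"). The sentence naming the ANOVA calls it an intragroup analysis. A one-factor ANOVA with post hoc contrasts across three arms is a between-group comparison, and it is read that way here.

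**The concern.** A sample size belongs to one particular test. The calculation is described as "in a unilateral contrast", which is directional. The planned ANOVA F test has no direction, and Bonferroni correction lowers the significance level of each pairwise comparison. If the 90% was worked out for a simpler and more lenient test, it does not describe the trial's chance of success.

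The Secondary objective asks how the respiratory programme compares with the toning programme and with sham. Those are pairwise questions, and the overall F test cannot answer them. If a contrast came out non-significant, readers would take it as a miss by a trial with a 10% type II error, when the error for that contrast is larger. It is also unclear whether the 90% goes with 32 or with 38 per group.

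**Working it through.** **Inputs, all from the sample size section:** alpha 0.05, one-sided; power 0.90; SD 0.125; difference 0.10, so d = 0.10/0.125 = 0.8; loss 15%; 32 per group stated; 38 per group (114 in total) enrolled.

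**Step 1: reproduce 32.** Two groups, one-sided:

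n = 2(1.645 + 1.282)² × (0.125/0.10)² = 26.8, so 27 evaluable. Then 27/0.85 = 31.8, so 32. This matches exactly.

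The alternatives tried do not give 32:

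| Basis for 90% power | Evaluable per arm | After 15% loss |
|---|---|---|
| Two groups, two-sided 0.05 | 33 | 39 |
| One-way ANOVA, third mean midway | 41 | 49 |
| One-way ANOVA, two arms equal | 31 | 37 |
| Two groups, two-sided 0.05/3 (normal formula) | 43 | 51 |

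The mention of three groups therefore has no effect on the number: a two-group figure has been used for each of three arms.

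**Step 2: evaluable patients under the planned enrolment.** 38 × 0.85 = 32.3, so 32 per arm after the planned loss, or 38 with none.

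**Step 3: power of one Bonferroni contrast.** Noncentral t with the pooled three-arm variance, 3n − 3 degrees of freedom and noncentrality 0.8 × √(n/2). Two assumptions: tests are two-sided, and all three pairs are compared, so each is tested at 0.05/3.

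- n = 32: noncentrality 3.20, critical value 2.44 on 93 df, power 77.5%.
- n = 38: noncentrality 3.49, critical value 2.43 on 111 df, power 85.3%.

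Simulation (40,000 replicates) gave 77.6% and 85.2% to 85.3%. Requiring a significant F test as well changes these by less than half a percentage point.

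**Step 4: power of the overall F test.** Noncentral F with 2 and 3n − 3 df, and a largest difference of 0.8 SD:

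| Evaluable per arm | Third mean midway | Two arms equal |
|---|---|---|
| 32 | 81.2% | 91.3% |
| 38 | 87.9% | 95.4% |

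**Step 5: what 90% per contrast would take.** By the method of Step 3, 44 evaluable per arm, which is 52 randomised per arm (44/0.85 = 51.8) or 156 in total. With 32 evaluable, 90% power is reached at 0.933 SD: 0.933 × 12.5% = 11.7%, against the 10% in the plan.

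**The case against.** Four points can be made for the plan.

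*The arithmetic is right, and the margin is generous.* This stands. The 32 is correct for its own inputs, so there is no slip in the calculation. Enrolling 38 recovers part of the shortfall. A reader might infer that power is as low as 69%, but that figure belongs to 27 evaluable out of 32 randomised per arm, and the article enrols at least 38.

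*The F test can reach 90%.* This stands in part. It does so if two arms have equal means (91% at 32 evaluable), but not if the third mean lies midway (81%). A reader might take 78% as the power of the ANOVA. It is the power of one contrast.

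*Two-sided tests and three pairs are assumptions.* This also stands. The only statement of sidedness in the article is the one-sided basis of the sample size, and the number of contrasts may be fixed in a document not shown. Milder readings narrow the gap. At 32 and 38 evaluable, two two-sided contrasts (0.025 each) have 82% and 89% power, and three one-sided contrasts (0.05/3 each) have 85% and 91%. None of these reaches 90% at the planned 15% loss.

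*No estimate, interval or type I error is affected.* This is true, and readers will have the confidence intervals. It limits the harm to a misstated power.

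A reader might also infer that the 15% was counted twice, since 32/0.85 = 37.6, which rounds up to 38. The article does not say how 38 was reached. If that is the explanation, it added patients and power and did no harm.

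**Conclusion.** The concern holds in a limited form. The stated 90% belongs to a one-sided comparison of two groups, not to the ANOVA with Bonferroni contrasts to which the Statistical analysis section attaches it. For the contrasts that answer the trial's question, power with 38 per arm is about 78% after 15% loss and about 85% with none. The type II error is therefore about 22% or 15%, against a stated 10%.

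These figures rest on the plan's 0.8 SD difference, two-sided tests, three pairs and normally distributed data. The size of the shortfall depends on those choices. The mismatch between the sizing basis and the planned test does not.

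**What to change.** Keep 114 patients and change the wording in both sections.

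- Sampling and sample size calculation: remove the one-sided contrast as the sizing basis. Drop 32 as the required number, and give 38 randomised per arm, 32 evaluable after a 15% loss applied once, as the single target. Replace the 10% beta risk with the power of the planned contrast.
- Statistical analysis: replace the 90% with the same statement, and say that the contrasts are two-sided and how many pairs are compared.

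Suggested text: *With 38 patients per arm (32 evaluable after 15% loss), each two-sided Bonferroni-adjusted pairwise contrast has about 78% power for a 10% difference (SD 12.5%), or 90% power for a difference of about 11.7%.*

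If fewer pairs or one-sided tests are intended, that should be stated and the power recalculated on that basis. The cost is a less favourable power statement; no patients or visits are added.

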### Randomization

Patients will be divided into three groups by means of balanced randomization, carried out with free software (http://www.randomized.org/). The randomization sequence will only be performed by the principal investigator and auditor. No participant in the study will have access to the randomization sequence, which will be hidden and saved, to guarantee a correct randomization with security.

### Blinding

Evaluator and patients in the study will be blinded during the entire process. The evaluator will be unaware of the study objectives and the randomized distribution of patients to study groups and will not have access to the randomization sequence. Meanwhile, although blinding for patients will not be possible to achieve it completely, subjects will be unaware of other treatment modalities, and they will not know if they belong to the intervention or sham group.

### Statistical analysis

The statistical analysis will be carried out through the IBM-SPSS Statistics 24 software, considering the Kolmogorov-Smirnov test as the standard normality test. We will analyze the intragroup hypothesis contrast inference by Student’s *t* test for paired variables with parametric distributions and Kruskal-Wallis *H* for non-parametric distributions. We will analyze the intragroup hypothesis contrast inference by one-factor ANOVA in the case of parametric distributions and Kruskal-Wallis *H* for non-parametric distributions. We will apply a posteriori analysis (post hoc) through Bonferroni’s contrast for parametric distributions and Mann-Whitney’s *U* for non-parametric ones. The confidence level used will be 95% (0′05), and the power of the study will be 90% (0′1). If the rate of loss to follow-up were observed greater than 15%, we will perform an intention-to-treat analysis.

A sub-analysis will be carried out, depending on the age of the patients, sex, and autonomous community of residence.

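### A normality test on the trial data chooses between means with Bonferroni and ranks with no stated correction, outcome by outcome, although the trial is sized on mean VASF

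*Protocol article*

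**What the plan says.** All of this is in the protocol article, under Statistical analysis unless stated.

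- The normality check is fixed by "considering the Kolmogorov-Smirnov test as the standard normality test".
- The comparison across the three arms is "one-factor ANOVA in the case of parametric distributions and Kruskal-Wallis *H* for non-parametric distributions". The sentence calls this intragroup, but ANOVA across three arms only makes sense between groups, and it is read that way here.
- Pairwise follow-up on the parametric route: "We will apply a posteriori analysis (post hoc) through Bonferroni’s contrast for parametric distributions".
- Pairwise follow-up on the other route: "Mann-Whitney’s *U* for non-parametric ones". No multiplicity correction is attached to it.
- The section does not say whether pairwise tests are run only after a significant overall test.
- No outcome is given a default analysis, and this includes VASF.
- Under Sampling and sample size calculation, the trial is sized on VASF: a difference of 0.10, SD 0.125, one-sided alpha 0.05, power 90% and 15% losses, giving 32 per arm. Recruitment is set at 38 per arm, 114 in total.

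**The concern.** The normality result settles three things at once for each outcome: which test is used, whether means or ranks are compared, and whether a correction for three contrasts is stated. Only one route compares the quantity the trial was sized for. Two outcomes in the same report could be judged by different kinds of effect and to different error standards, for no reason other than a preliminary test result.

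The effect on false positives also needs sizing. Three uncorrected pairwise tests are more permissive than three Bonferroni contrasts, and the permissive route is the one taken when scores are skewed. That is plausible for a 0-10 fatigue scale in a trial that recruits only mild cases.

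**Working it through.** **1. What the sample size compares.** Inputs are from Sampling and sample size calculation: difference 0.10, SD 0.125, one-sided alpha 0.05, power 0.90, losses 15%.

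n = 2 × (1.645 + 1.282)² × (0.125/0.10)² = 26.8, so 27 per arm. Then 27/0.85 = 31.8, so 32. This reproduces the protocol's 32 and shows that the trial is sized for a difference between two means. Only the parametric route tests that. At 38 recruited, 15% losses leave 38 × 0.85 = 32.3, so about 32 evaluable per arm.

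**2. Nominal familywise error for three contrasts.** Uncorrected: 1 − (1 − 0.05)³ = 0.143. Bonferroni: 1 − (1 − 0.05/3)³ = 0.049. Both formulas treat the contrasts as independent. They share arms, so simulation is the better guide.

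**3. Simulation under the global null, three arms of 32.** Assumptions not given by the protocol: Kolmogorov-Smirnov applied in each arm at 0.05, any rejection sends the outcome to the rank route, two-sided pairwise tests, and the distributions shown. Gated means that a pair counts only if the overall ANOVA or Kruskal-Wallis test is also significant. The first table has 3,000 trials per row and uses critical values for estimated parameters (Lilliefors).

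| Distribution | Rank route taken | Any Mann-Whitney pair | Any Bonferroni t pair | Rule as written, ungated | Rule as written, gated |
|---|---|---|---|---|---|
| Normal | 13.3% | 10.7% | 4.1% | 5.1% | 3.9% |
| Normal, mean 2, SD 2, cut at 0 and 10 | 49.4% | 12.8% | 4.6% | 10.2% | 5.1% |
| Lognormal, log-SD 0.5 | 86.9% | 12.3% | 4.2% | 11.6% | 5.5% |
| Exponential | 99.5% | 12.3% | 3.6% | 12.3% | 4.7% |

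The second table has 1,500 trials per row. The SD of 1.25 is the protocol's 12.5% placed on the 0-10 scale.

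| Distribution | Rank route: plain / Lilliefors | Ungated error: plain / Lilliefors |
|---|---|---|
| Mean 1, SD 1.25, cut at 0 | 3% / 80% | 4.7% / 10.3% |
| Exponential | 37% / 99% | 8.4% / 12.9% |
| Mean 2, SD 1.25, cut at 0 | not tabulated / 13% | not tabulated / about 6% |

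Monte Carlo standard error at 10% is √(0.10 × 0.90/1,500) = 0.8 points. Repeat runs of the mean-1 Lilliefors case, with 600 to 3,000 trials, gave 8% to 12.3%. Runs of 600 trials at means 2, 3 and 5 gave 4-6% ungated error with Lilliefors values and 3-5% with plain values.

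**4. Why the assumed mean matters.** The share of scores piled at 0 is Φ(−mean/SD). It is Φ(−0.8) = 21% for mean 1 and SD 1.25, Φ(−1.0) = 16% for mean 2 and SD 2, and Φ(−1.6) = 5% for mean 2 and SD 1.25. The Lilliefors rank route follows that share: 80%, 49% and 13%.

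**5. Overall test.** The two-stage choice of ANOVA or Kruskal-Wallis had an error of 4-6% in the 1,500-trial runs. ANOVA used throughout had 3.9-5.3%, exponential data included. At this arm size ANOVA does not need the preliminary test to protect its error rate.

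**6. One arm truly different by 0.8 SD (normal data, 3,000 trials).** Error on the remaining null pair was 4.6% for gated Mann-Whitney and 1.4% for gated Bonferroni t. With three arms, a gate is sufficient control.

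**The case against.** The strongest reply is that the plan is pre-specified. It names the normality test, the test on each route and the follow-up on each route. A reader might infer that analysts choose the method after looking at results. The text does not support that: only the route taken depends on the data, and the link from the normality result to the route, though implied by sentence order, is the only sensible reading.

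Second, pairwise tests described as post hoc and placed straight after the overall test may be meant to follow only a significant overall result. A reader might infer that familywise error is certainly inflated. That does not follow, since with a gate it stays near 5%. The section states no gate, however, and it states a correction on one route only.

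Third, the larger figures need skew or a floor. The protocol gives no mean for VASF, and moving an assumed mean from 1 to 2 at SD 1.25 removes nearly all the excess. This stands, and it is why the size is given as a conditional range.

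Fourth, plain versus Lilliefors critical values is a software-level detail that a journal article may leave to the analysis plan. This also stands. The contrast in the second table shows how unstable the route is, but the missing detail is not itself a fault.

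What survives is that the article states this rule and fixes it badly. It is not a matter merely left for later.

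**Conclusion.** The defect is real and moderate. For VASF, the outcome the trial is sized on, the test, the quantity compared and the multiplicity control are all left to a preliminary test, and only one route matches the sample size. This holds whatever the error rates are.

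The cost in false positives is conditional. The overall between-arm test is sound at about 5%. Familywise error across the three contrasts reaches about 8-13% only when three things coincide: strong skew or a floor, the rank route, and ungated Mann-Whitney pairs. With gating it is about 3-6%, and at mean 2 with SD 1.25 the ungated figure is about 5-6%. All these figures rest on per-arm testing at 0.05 and on assumed distributions.

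Two further inferences should be avoided. The preliminary test does not corrupt the overall ANOVA or Kruskal-Wallis comparison. Nor would removing it settle the primary comparison completely: under Outcome measures every outcome is recorded daily for 21 days, so the time point of the comparison is a separate question.

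**What to change.** - Stop using the normality test to choose the analysis. Use normality checks only to describe residuals.
- Name one between-arm comparison of means, adjusted for the baseline value already collected, for each of VASF, FEV1, PEF, 6MWT and 30STST.
- Name one fixed analysis each for the Borg Scale and MD12. These are bounded scores, where the choice between means and ranks matters most.
- Apply one correction, for example Bonferroni or Holm, to the three pairwise contrasts whichever test is used.
- Keep the rank-based test, with the same correction, as a stated sensitivity analysis.

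Baseline adjustment is a further improvement and is not needed to repair the defect. The single correction is what repairs the error rate.

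The cost is a few sentences and one sensitivity run, with no change to conduct or data collection. Means stay primary even when a scale is skewed, and corrected rank contrasts are slightly less powerful than uncorrected ones. For contrasts of means, Bonferroni is already the protocol's rule on the parametric route. At 32 evaluable per arm and the design difference, one-sided power is 94.0% uncorrected and 85.8% at 0.05/3 (79.0% if two-sided), before any gain from baseline adjustment.

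### Kruskal-Wallis is named as the non-parametric alternative to the paired t test; it ignores the pairing, so the within-group test is too conservative and loses power

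*Protocol article*

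**What the plan says.** The Statistical analysis section chooses between a parametric and a non-parametric branch by a Kolmogorov-Smirnov test and then sets three rules.

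- **Within-group contrast.** Student's t "test for paired variables with parametric distributions and Kruskal-Wallis" H for non-parametric distributions.
- **Second contrast, also labelled intragroup.** "We will analyze the intragroup hypothesis contrast inference by one-factor ANOVA in the case of parametric distributions and Kruskal-Wallis" H for the non-parametric case.
- **Post hoc.** Bonferroni's "contrast for parametric distributions and Mann-Whitney" U for the other branch. No adjustment is attached to Mann-Whitney, and no sentence says that the post hoc tests depend on a significant overall test.

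The Outcome measures section has every outcome measured daily for 21 days on the same patients. Neither the Wilcoxon signed-rank test nor the Friedman test appears anywhere in the article.

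**The concern.** A paired t test works on each patient's own difference. Its rank counterpart must do the same. Kruskal-Wallis on baseline and follow-up values treats them as two separate samples of patients. If a patient's values are positively correlated, the test uses too large a variance for the difference, rejects too rarely under the null and misses changes that a paired test would find. The normality check would then decide whether the pairing is used at all.

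The article's primary objective concerns the respiratory effects of an exercise programme, and the comparison among arms is the secondary objective. The within-group contrast is therefore not a side issue in this plan, even though it is not the randomised comparison.

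Two smaller matters sit in the same paragraph. The word *intragroup* appears twice, the second time beside tests for independent groups. Pairwise error control is stated for one branch only.

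**Working it through.** **1. The plan's own figure.** The Sampling and sample size calculation section assumes "an alpha risk of 5% (0.05), a beta risk of 10% (0.10), in a unilateral contrast", with "a typical deviation of 12.5% (0.125), a minimum difference to detect of 10% (0.10"). For two independent means:

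n = 2 × (1.645 + 1.282)² × (0.125/0.10)² = 26.8, rounded up to 27 per group. With 15% losses, 27/0.85 = 31.8, rounded up to 32.

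The stated 32 per group is reproduced. It is a between-group calculation and does not depend on the within-group test. Planned enrolment is 38 per group, and 38 × 0.85 = 32.3, so about 32 pairs per group is a sensible size for the check.

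**2. Why the test is conservative.** Let ρ be the within-patient correlation. For two measurements with equal variance σ², the mean difference has variance 2σ²(1 − ρ)/n, but an independent-samples test uses 2σ²/n. Under the null its standardised statistic has standard deviation √(1 − ρ) instead of 1. As an approximation that carries over to ranks, the true type I error is 2 × [1 − Φ(1.96/√(1 − ρ))]. At ρ = 0.5 the argument is 1.96/0.707 = 2.77, which gives about 0.6%. At ρ = 0 it is 5%.

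**3. Simulation.** Bivariate normal pairs, two-sided 5%, 32 pairs. The documents give neither the correlation nor a within-group shift, so both are assumptions and a range is shown. The type I error and 0.5 SD columns use 4,000 runs, the 0.8 SD column 2,000. The 0.8 SD shift is the plan's own standardised difference, 0.10/0.125, although the plan sets it for a difference between groups. Each cell shows Kruskal-Wallis against signed-rank.

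| Correlation | Type I error | Power, 0.5 SD | Power, 0.8 SD |
|---|---|---|---|
| 0 | 4.9% vs 4.7% | 48% vs 47% | no loss |
| 0.3 | 2.0% vs 5.0% | 48% vs 62% | 91% vs 96% |
| 0.5 | 0.7% vs 4.7% | 48% vs 76% | 93% vs 99% |
| 0.7 | 0.2% vs 4.3% | 48% vs 93% | 97% vs 100% |

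Separate runs at correlation 0.5 put the Kruskal-Wallis type I error between 0.4% and 1.0%, and power at 0.5 SD at 48% to 49% against 76% to 77%. With 38 pairs and correlation 0.5, type I error is 0.9% against 5.2%. Power is then 59% against 83% at 0.5 SD and 97% against 100% at 0.8 SD.

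**4. Post hoc tests.** Three arms give three pairwise comparisons. If they were independent, familywise error would be 1 − 0.95³ = 14.3%. They share arms, so it is lower. Simulated under the global null (10,000 runs) with 32 and 38 per group:

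| Rule for Mann-Whitney | 32 per group | 38 per group |
|---|---|---|
| Unadjusted, read on their own | 11.7% | 11.9% |
| Bonferroni, 0.05/3 = 0.0167 | 3.9% | 4.1% |
| Unadjusted, only after a significant Kruskal-Wallis | 4.5% | 4.8% |

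**The case against.** The strongest reply is that this is loose wording in a condensed article and does little harm. Much of that stands.

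- **No false claims of benefit.** The error is conservative under positive correlation. It cannot manufacture a within-group effect, and it does not touch the randomised comparison, for which Kruskal-Wallis is a proper choice.
- **The loss depends on the inputs.** At 0.8 SD power stays above 90% for correlations of 0.3 to 0.7. The large losses belong to smaller shifts, and those are assumed.
- **Use of the non-parametric branch is uncertain.** Fatigue is scored on a bounded 0 to 10 line, so non-normality is possible, but the article gives no distribution from which to call it likely.

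Three stronger readings are tempting, and the article does not support them.

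- *That no between-group test is specified.* The second sentence does say intragroup. But the Abstract says the hypotheses will be tested between the groups, the within-group test has just been given, and one-factor ANOVA with pairwise post hoc contrasts makes sense only across the arms. It is a slip for *intergroup*.
- *That Mann-Whitney is a wrong test.* It is valid for comparing two independent arms. Only the adjustment is unstated.
- *That familywise error will be about 12%.* That requires the pairwise tests to be read regardless of the overall test. The article calls them post hoc, which may imply a significant Kruskal-Wallis first. With exactly three groups that condition holds the error near 5%.

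The reply does not rescue the paired-data rule. The sentence itself says the variables are paired, so swapping intra for inter cannot repair it, and Kruskal-Wallis is assigned again in the next sentence, where it fits. This is a stated rule that is wrong, not a detail left to a fuller document.

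**Conclusion.** The concern holds for the within-group non-parametric branch: the named test is wrong for paired data. With 32 pairs and an assumed correlation of 0.5, it runs at about 0.4% to 1% instead of 5%, with power of about 49% against 77% at an assumed 0.5 SD shift and about 93% against 99% at 0.8 SD. The loss vanishes at zero correlation. At 0.5 SD it grows as correlation rises. These figures assume bivariate normal data and a comparison of two time points.

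The second *intragroup* is a labelling slip. The missing statement about Mann-Whitney is a secondary point: about 12% familywise error if the tests are unadjusted and unconditional, and about 5% or below with either remedy. A reader might infer that the sample size is undermined. It is not: 32 per group reproduces and rests on a between-group comparison.

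**What to change.** Amend one paragraph of the Statistical analysis section.

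1. For the within-group contrast, replace Kruskal-Wallis with the Wilcoxon signed-rank test, or the Friedman test if more than two time points are compared.
2. In the sentence on one-factor ANOVA and Kruskal-Wallis, change *intragroup* to *intergroup*.
3. For the Mann-Whitney post hoc tests, either apply Bonferroni at 0.05/3 as in the parametric branch, or state that they are run only after a significant Kruskal-Wallis test.

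The cost is a few words. The named software offers all these tests, and no change in sample size follows. If Bonferroni is chosen, the adjusted Mann-Whitney p-values will be slightly less favourable.
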